### Recruitment

Patients will be recruited from regular referrals to a mental health care center specialized in PD in Amsterdam (at two locations) in the Netherlands. Recruitment is planned for 2 years. During intake assessment, patients will be screened by the intake clinician on the in- and exclusion criteria. Patients who are eligible based on this screening will be approached by the research assistant. Patients who are excluded or not willing to participate will be referred to one of the regular treatment modalities by the intake clinician. In Fig. 1 an overview of the trial flow diagram is provided.

**Fig. 1 Fig1:**
[figure not shown]
Trial flow diagram

### Randomization and procedure

An independent research assistant will contact eligible patients within a week after intake and will invite the patient for research assessment. Additional information about the study is provided by email, giving the patient the time to consider participation. During the assessment meeting any doubts or questions about participating in the study can be discussed with the research assistant. The MINI-plus (section A and B) and the BDI-II will be assessed during research assessment and if no structured diagnostic interview has been completed during intake, the SCID-II / SCID-5-PD will be conducted. If the patient is eligible and willing to participate an informed consent is signed. Patients will then be randomized by one of two research department employees in one of four groups (with a 1:1:1:1 allocation) using a computer script performing block randomization (25 vs 50-sessions; ST vs SPSP). Randomization will be pre-stratified according to depression severity (BDI-II < =29 low, BDI-II= > 30 high). Treatment starts as soon as possible (approximately within 0 to 3 months) and patients are assigned to a therapist based on the allocated condition and the therapists availability. Patients will be assigned for the online baseline assessment in the week prior to the start of therapy. During the course of treatment patients will be requested to fill in short online assessments at 1, 2 and 3 months. At 6 months, end of treatment and follow-up extra questionnaires are added. The data collection process is monitored in detail and patients who don’t fill out the questionnaires will be reminded by the research assistant. In addition to the online measurements the SCID-II / SCID-5-PD and MINI-plus (section A and B) will be assessed at treatment termination (9–12 months) and follow-up (21–24 months) by a research assistant who is blind for condition. All data collected from interviews during research assessment at baseline, end of treatment and follow up will be entered and stored on site. Online submitted data forms are converted to the onsite database by the data analyst. All online submitted data will be checked by a research assistant on missing data or specific errors. Independent random data checks will be conducted on entry and encoding errors. All data is entered electronically. As part of the analysis, standard checks on double data entry and range checks on data values will be performed.

Therapists are requested to fill in online assessments at 1, 2, 3 and 6 months and at treatment termination concerning the therapeutic relation, the levels of discourse in SPSP and the dominant schema modes in ST. Participants may withdraw from the study for any reason at any time. Discontinuation of the treatment can also be indicated for serious clinical reasons as concluded in consultation meetings (i.e. immediate need for hospitalization or immediate need for an additional intervention leading to considerable exceedance of the assigned psychotherapy dosage). Early discontinuation of the treatment is not a reason for withdrawal from the study: these patients will be seen for an exit-interview and will be asked to continue participating in all remaining assessments. Participants have access to post-trial care if necessary for substantial clinical reasons during follow up period. An overview of all self-report measures and semi-structured interviews is presented in Table 2. All therapist and observer ratings per assessment are presented in Table 3.

**Table 2 Tab2:** Overview of patient instruments per time point (months)

Instruments/months	I	A	0	1	2	3	6	END	FU 6 m	FU 12 m
Clinical outcomes										
Depression										
BDI-II		X	X	X	X	X	X	X	X	X
MINI plus, section A/B		X						X		X
Personality										
SIPP	X					X^a^	X	X	X	
SCID-screener	X							X		X
SCID-II / SCID-5-PD		X						X		X
YSQ-sf			X			X^b^	X	X		X
SMI			X			X^c^	X	X		X
DPI			X				X	X		X
Quality of life										
EQ-5D(5 L)			X			X	X	X		X
Happiness question			X	X	X	X	X	X	X	X
Cost-effectiveness										
Trimbos/iMTA Tic-P			X				X	X	X	X
Process/Predictors										
WAI-S				X	X	X	X	X		
Other measures										
Demografics	X									
Treatment history			X							
BSI	X		X			X	X	X		X
OQ-45	X					X	X	X		X

*I* Intake, *A* Assessment, *0* Start of therapy, *1/2/3/6* Months in therapy, *END* End of therapy (at 8–12 months), *FU 6 m* Follow-up at 6 month after end of therapy, *FU 12* Follow up at 12 months after end of therapy. ^a^SIPP subscale Relational Capacities, ^b^YSQ-sf subscales Emotional Deprivation and Failure, ^c^SMI subscales Healthy Adult, Happy Child and Detached Protector

**Table 3 Tab3:** Overview of therapist and observer instruments per time point (months)

Instruments/months	I	A	0	1	2	3	6	END	FU 6 m	FU 12 m
Process/Predictors										
WAI-S				X	X	X	X	X		
Modes/Level of discourse				X	X	X	X	X		
Other measures										
End of treatment questionnaire								X		

*I* Intake, *A* Assessment, *0* Start of therapy, *1/2/3/6* Months in therapy, *END* End of therapy (at 8–12 months), *FU 6 m* Follow-up at 6 month after end of therapy, *FU 12* Follow up at 12 months after end of therapy

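### The visit labelled baseline falls after randomisation; the BDI-II already taken before randomisation should be named as the reference for the primary analysis

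*Protocol article*

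**What the plan says.** Randomization and procedure gives the sequence. First comes the research assessment: "The MINI-plus (section A and B) and the BDI-II will be assessed during research assessment". After eligibility and consent, "Patients will then be randomized by one of two research department employees in one of four groups", and "Randomization will be pre-stratified according to depression severity", with BDI-II scores split at 29/30. Next, "Treatment starts as soon as possible (approximately within 0 to 3 months) and patients are assigned to a therapist based on the allocated condition" and on therapist availability. Only after that: "Patients will be assigned for the online baseline assessment in the week prior to the start of therapy".

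The same section also applies the word to the interviews done before randomisation: "All data collected from interviews during research assessment at baseline, end of treatment and follow up will be entered and stored on site". The Instruments section likewise speaks of baseline screening when it describes the eligibility interviews.

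Table 2 lists the BDI-II at both A (assessment) and 0 (start of therapy). Data analyses plans an intention-to-treat analysis of the BDI-II by mixed models with a growth curve, and a reliable change analysis. It does not say from which BDI-II either one starts.

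**The concern.** A baseline earns its place in a randomised comparison because allocation cannot have affected it. The score the article labels as the online baseline does not have that guarantee. It is taken after allocation, at a date tied to the start of therapy, on a self-report scale, in a trial where patients cannot be masked to how often they attend. Hope or disappointment about the number of sessions, or ordinary change during the wait, could already be in it.

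The reference score matters here because the primary hypothesis is a stronger reduction in depression severity, and because both the growth curve and reliable change need a starting value. If the time-0 score is that value, a post-randomisation difference between the dosage groups at time 0 is subtracted out or adjusted away as if it had been there by chance before the trial began.

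**Working it through.** **1. Order of events (Randomization and procedure; Table 2).**

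| Step | Event | BDI-II |
|---|---|---|
| 1 | Research assessment | A |
| 2 | Consent | – |
| 3 | Randomisation, stratified on BDI-II | – |
| 4 | Therapist assigned; wait of about 0 to 3 months | – |
| 5 | Online baseline, in the week before therapy | 0 |
| 6 | Start of therapy | – |

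Table 2 has no BDI-II at intake. The only BDI-II that exists when patients are stratified is therefore the one at A.

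**2. First measurement of each instrument (Table 2).**
- Before randomisation: BDI-II, MINI-plus and the SCID interview at A; SIPP, SCID-screener, BSI and OQ-45 at intake. The BDI-II and BSI are repeated at 0.
- First at time 0, after randomisation: YSQ-sf, SMI, DPI, EQ-5D-5L, happiness item and TiC-P.

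A patient who is randomised but never starts therapy thus has a pre-randomisation BDI-II and MINI-plus, and lacks a starting value only for the second list. The EQ-5D-5L and TiC-P feed the 24-month economic evaluation. Multiple imputation is planned there, but it cannot turn a time-0 value into a pre-randomisation one.

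**3. How a shift at time 0 would carry through.** Let d be the true effect at the end. Let s be a difference between the dosage groups at time 0 that arose after randomisation, in SD units and in the direction of the effect. Let ρ be the slope of outcome on the time-0 score.
- Change from time 0 shows d − s.
- Adjustment for time 0 shows d − ρs.
- Adjustment for A carries no such term, because allocation cannot have moved the score at A.

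The document gives neither s nor ρ. To show the mechanism only, take the planning value d = 0.45 (Sample size) and assume s = 0.05 to 0.20 and ρ = 0.3 to 0.7:
- change from time 0: 0.45 − 0.05 = 0.40 down to 0.45 − 0.20 = 0.25;
- adjustment for time 0: 0.45 − 0.3 × 0.05 = 0.435 down to 0.45 − 0.7 × 0.20 = 0.31.

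A shift in the other direction inflates the effect by the same amounts, and s = 0 gives no bias. These figures are not evidence that a shift occurs. Nor does Data analyses specify a change score or an ANCOVA. A growth curve that starts at time 0 reads the effect as departure from that point, so it would be exposed in part.

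**4. Sample size.** The planned figure reproduces: 2 × (1.96 + 0.842)² / 0.45² = 77.5, so 78 per dosage group. The calculation does not depend on which BDI-II is the baseline, so the fix leaves it as it is.

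**The case against.** The strongest reply is that the choice of reference score belongs in a statistical analysis plan, which is not shown, and that a mixed model over repeated BDI-II scores need not use time 0 as a covariate at all. Silence alone would indeed be no finding. But the article is not merely silent: it attaches the word baseline to the post-randomisation visit, and an analyst who follows that wording would take the time-0 score.

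A second reply is that measuring just before therapy and counting months in therapy suits a question about dosage and process. That stands. Nothing here requires the time-0 assessment to be dropped or the time axis to be moved to randomisation.

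Two further limits also stand. The article does not say when patients learn their allocation. It gives a single waiting range for everyone and describes therapists by type of therapy rather than by dosage, so nothing shown implies that waits differ between 25 and 50 sessions.

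A reader might also infer that patients who never start therapy have no baseline and drop out of the analysis. The document does not support this. Their BDI-II and MINI-plus are taken before randomisation, the analysis is stated as intention-to-treat, and no section excludes them. The rule on continued assessment after early discontinuation does not mention never-starters, but that is silence and not exclusion.

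**Conclusion.** The point holds in a limited form. The label baseline covers two time points, one of them after randomisation, and the reference BDI-II for the primary model and for reliable change is not fixed. A bias through the time-0 score is possible, given unmasked treatment and a self-reported outcome, but it is not shown. Its size and direction cannot be derived from the document, and neither can the number of never-starters. Several secondary and economic measures have no pre-randomisation value at all; the primary outcome does. The change is worth making because it removes a route for bias using a score that is already collected.

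**What to change.** - In Data analyses, define the BDI-II at the research assessment (Table 2, column A) as the baseline for the primary mixed model, either as a covariate or through a constrained baseline, and as the starting score for reliable change.
- Treat the time-0 BDI-II as a post-randomisation measurement, and rename the online assessment so that baseline means one time point throughout.
- State that all randomised patients, including those who never start therapy, stay in the intention-to-treat analysis with their BDI-II at A.
- State that the first YSQ-sf, SMI, DPI, EQ-5D-5L, happiness and TiC-P values are post-randomisation and are absent for never-starters.

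The cost is wording only: no extra BDI-II assessment and no change to the required 78 per dosage group.

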### Interventions

#### SPSP

SPSP is a supportive psychodynamic psychotherapy that uses a supportive stance and techniques to treat depression and to reduce depression vulnerability due to personality development. From a psychodynamic perspective SPSP emphasises the relational aetiology of and significance for the onset and recurrence of depressive symptoms. Current patterns of relationships are discussed and if appropriate related to interpersonal experiences that stem from the past and act as a mould for new relationships, both with others and oneself. The supportive stance and techniques contribute to the hypothesized working factor of SPSP: Adequate Psychoanalytic Support (APS). APS aims at fostering progression and countering regression by adequately gratifying unmet developmental needs in patients. SPSP has originally been tested for a broad group of depressed patients [37] in a dosage of 16 sessions. For patients with both depression and PD the therapy has now been intensified to either 25 or 50 sessions in 1 year.

In SPSP the therapist uses as a reference eight levels of discourse (i.e. levels of insight attainable by the patient) that serve to structure and foster the therapeutic process. As seen in Fig. 2 level one and two focus on the depressive symptoms and the influence of life circumstances on these symptoms. Interventions at these levels are mainly supportive, directed at behavioural activation, encouraging adaptive coping mechanisms, reducing feelings of guilt or giving praise or advice. At the third level the focus shifts to current relationships. At the fourth level patterns in these relations are discussed that may contribute to the onset or persistence of depressive feelings. Then, at the fifth level, the focus proceeds to the patient’s own contribution to the ongoing existence of these patterns. The sixth level focuses on an etiologic explanation to this contribution and how past relational experiences influence the patient’s current life. At the seventh level, the relationship the patient maintains with himself (for instance self-esteem regulation) is discussed as a consequence of identification with past internal-interpersonal relational experiences. Level eight concerns the relationship with the therapist and transference manifestation. At the higher levels the therapy is focusing more on personality functioning and the therapist uses more interventions to facilitate insight. The discourse levels are an attempt to structure the steps in the therapeutic process and to find the most helpful focus for the patient. The goal of SPSP is not to reach the highest level of insight, but to meet the patient on the level of insight he is capable of and which helps diminish the depression and improve interpersonal and intrapersonal functioning. SPSP can be placed on a variable point on the expressive- supportive continuum as the therapist is allowed to adopt a more supportive or more interpretative stance. In the second half of the therapy the frequency of the therapy sessions decreases, matching the developed growth, acquired insight and internalized adequate psychoanalytic support and stimulating the patient to integrate these in daily live (Fig. 2).

**Fig. 2 Fig2:**
[figure not shown]
Levels of discourse in SPSP

#### Schema therapy

Schema therapy is an integrative psychotherapy combining experiential, cognitive-behavioral, psychodynamic and interpersonal techniques [15]. Schemas can develop after basic emotional needs have not been met in early life. A schema mode is an emotional state in which one or more schemas are active and often has its particular coping strategy, once developed to protect oneself, but eventually causing more harm than good. The goal in ST is to develop the healthy adult mode by reducing harmful coping modes, battling the punitive (self-criticizing) and demanding modes and teaching patients how to meet and be met in their emotional needs. Following the development of ST, the focus in ST in the current study is on mode work [38]. The ST protocol for chronic depression [17] is used and adapted to fit the current study in terms of number of sessions and session frequency.

The therapy is divided into three phases. In the assessment and exploration phase the patient learns to understand the schema modes both cognitively and emotionally, their etiology and their interaction with depression. Techniques specifically used in this phase are psycho-education and diagnostic imaginations. Although a shorter period is often sufficient, this phase will take a maximum of 7 weeks (accounting for 7 weekly sessions in the 25 sessions condition and 14 twice weekly sessions in the 50 sessions condition).

In the second phase several techniques can be used to achieve change on cognitive, emotional and behavioral levels using cognitive techniques, experiential techniques such as chair work and imagery rescripting, behavioral techniques and techniques focusing on the therapeutic relationship such as empathic confrontation. The therapist has the role of a good parent, thereby providing a safer, warmer and more predictable environment than most patients have experienced early in life. As the healthy adult mode and the patients autonomy is expected to develop, session frequency is lowered at the second half of this therapy phase. This phase will take approximately 17 weeks (accounting for 9 weekly sessions, followed by 4 sessions every 2 weeks in the 25 sessions condition; 18 sessions twice weekly, followed by 8 weekly sessions in the 50 sessions condition).

In the final phase of therapy behavioral change is aimed at and a relapse prevention plan will be developed in order to help the patient to get aware of risk factors for relapse and to address healthy actions when faced with these risk factors. Interventions are mainly focused on strengthening the healthy adult mode, autonomy and preparing for life after therapy. This last phase in therapy takes 10 weeks (accounting for 5 sessions every 2 weeks in the 25 sessions condition; 10 weekly sessions in the 50 sessions condition). An overview of the phase of the therapy and the corresponding session frequency is given in Fig. 3.

**Fig. 3 Fig3:**
[figure not shown]
Phases in ST for depression

#### Therapists

All therapists have an academic degree in Psychology or Psychiatry and are health care psychologists, psychotherapists, clinical psychologists or psychiatrists. All participating schema therapists are registered schema therapists in the Netherlands or schema therapists in training. When not yet registered the therapist has at least 6 months experience in ST and receives additional supervision. A 1 day training in ST for depression was given to all therapists in the ST condition by a registered supervisor in ST. The SPSP therapists are registered as SPSP therapists or in training. When not yet registered the therapist has at least 6 months experience in SPSP and receives additional supervision. All registered therapists in de ST or SPSP condition can consult each other in biweekly consultation meetings. All sessions are audio-taped for both supervision- and adherence-purposes.

#### Instruments

At baseline screening a research-assistant (MSc student holding a Bachelors-degree in clinical psychology or junior researcher, holding a MSc degree in clinical psychology; trained in SCID-II / SCID-5-PD and MINI-plus assessments) will conduct semi-structured interviews to verify whether the patient meets the inclusion criteria by diagnosing a depressive disorder and PD. At treatment termination and follow-up these interviews are repeated by a research-assistant blind to condition. In order to detect treatment effect the SCID-II / SCID-5-PD interviews at treatment termination and follow-up will cover the previous 6 months. A check on interrater reliability will be conducted for both SCID-II / SCID-5-PD and MINI at baseline and follow-up.

#### Clinical outcomes measures

##### Primary outcome: depression

***Beck Depression Inventory (BDI-II-NL)*** [39]. The BDI-II is a self-report instrument of 21 items assessing depressive symptoms during the last 2 weeks. The BDI is a strong screening instrument for the severity of depressive symptoms [40, 41] and is widely used for clinical and research purposes. It has shown good psychometric qualities for both the original [42] and the Dutch version [43].

***Mini-International Neuropsychiatric Interview (MINI-plus) section A (depression) and B (dysthymia)*** [44, 45]. The MINI-plus was designed as a structured interview for the major Axis I psychiatric disorders in DSM-IV and ICD-10. Until a DSM-5 version of the MINI-plus is available, section A and B of the MINI-plus will be assessed in order to diagnose DSM-5 depressive disorders at screening, termination and follow-up. The MINI-plus has acceptably high validity and reliability scores [46].

##### Secondary outcome: personality parameters

***Structured Clinical Interview for DSM-IV personality disorders (SCID-II)*** [47, 48]. The SCID-II is a semi-structured interview used to diagnose DSM-IV personality disorders. Both the original and the Dutch version have adequate to good interrater reliability and test-retest reliability [49, 50]. Following the transitioning to the DSM-5, the SCID-II interview will be replaced by the SCID-5-PD interview [51] to diagnose DSM-5 personality disorders.

Assessments using the SCID-II / SCID-5-PD will be guided by disorders previously affirmed by the patient on the SCID-PQ / SCID-5-SPQ (cut-off-1), a self-report questionnaire screening for personality disorders [52] that will be completed before the interview. Disorders not affirmed on the SCID-PQ / SCID-5-SPQ will be assumed to be true negatives, however if the assessment clinician has reason to assume false negatives further items will be assessed. This method is in accordance with instructions for using the SCID-II / SCID-5-PD and enables the assessment of personality disorder symptoms to be based upon self-report combined with a structured clinical interview.

***Severity Indices of Personality Problems (SIPP-118)*** [53]. The SIPP-118 is a dimensional self-report questionnaire measuring the severity of personality pathology by assessing the core components of adaptive and maladaptive personality functioning. Overall, the psychometric features of the SIPP are good, with evidence for good reliability (α coefficients ranging from .62 to .89, with a mean estimated score of .78), convergent validity and invariance of the factor structure [53].

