#### Secondary outcome: personality parameters

Measuring change in personality traits in the course of both dosage and therapy conditions will be done using (generalized) linear mixed models. Also the percentage of patients reaching reliable and clinically significant improvement on personality outcomes will be analyzed for both dosage and therapy conditions, using the method of Jacobson and Truax [69]. Comparison between the dosage conditions (and secondary between the therapy-conditions) will be analyzed using GEE. Finally, remission rates of personality disorders will be measured and compared for both conditions (and secondary for the therapy-conditions) with GEE at termination and follow-up (SCID-II / SCID-5-PD).

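### Assessor blinding protects the personality-disorder remission outcome only in part, because by default a self-report screener decides which disorders are examined at END and FU 12 m

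*Protocol article*

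**What the plan says.** All references are to the protocol article.

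- **Gate.** Under the instrument heading for the secondary personality outcomes, the SCID-II / SCID-5-PD interview is "guided by disorders previously affirmed by the patient on the SCID-PQ / SCID-5-SPQ (cut-off-1), a self-report questionnaire screening for personality disorders". The default for the rest is: "Disorders not affirmed on the SCID-PQ / SCID-5-SPQ will be assumed to be true negatives".
- **Override.** The same sentence continues: "however if the assessment clinician has reason to assume false negatives further items will be assessed". No criterion for such a reason is given.
- **Justification.** The article adds: "This method is in accordance with instructions for using the SCID-II / SCID-5-PD". It describes the result as self-report combined with a structured interview.
- **Timing.** In Table 2 the row "SCID-screener" is marked at intake, END and FU 12 m. The SCID interview is marked at the pre-treatment assessment, END and FU 12 m. Neither is scheduled at FU 6 m.
- **Blinding.** Under Instruments, at termination and follow-up "these interviews are repeated by a research-assistant blind to condition". Randomization and procedure likewise places the last interview at "follow-up (21–24 months) by a research assistant who is blind for condition". No one else is described as blind.
- **Use.** In the Data analyses section on personality parameters, "remission rates of personality disorders will be measured and compared for both conditions", by GEE at termination and follow-up.

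**The concern.** A screening gate serves a different purpose at entry than at outcome. At entry it saves time in finding disorders. At END and FU 12 m the question is whether a disorder already confirmed in this patient is still present, and the gate can settle that before the blinded assessor asks anything. The patient who answers the screener has attended either once or twice a week for the first months and so knows the dosage.

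At stake is the only interview-based personality outcome. The SIPP-118, YSQ-sf, SMI and DPI are all described as self-report. The Objective section hypothesises improvement in personality functioning at DSM-5 level, and the Discussion counts observer-rated personality measures among the study's strengths. To the extent that the gate decides the result, the one observer-rated personality measure becomes another self-report.

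**Working it through.** The plan gives no figure on this point, so there is none to reproduce. The check has two parts: reading the passages together, and an illustration with assumed inputs.

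**Reading the passages together**

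1. The gate is stated for SCID assessments in general, under an outcome heading, with no restriction to baseline.
2. Table 2 schedules the screener at both time points at which the SCID is repeated, so the gate is available there.
3. The Instruments section does adapt the SCID for outcome use, by having the later interviews cover the previous 6 months. It leaves the gate unchanged.
4. Nowhere does the article say that a disorder diagnosed at baseline is always re-interviewed, or that a baseline diagnosis counts as a reason to suspect a false negative.
5. The override is given to an assessment clinician, while the END and FU 12 m interviews are done by a research assistant. The article does not say who applies the override there.

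So a confirmed disorder that is no longer affirmed can be counted as remitted without blinded questioning.

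**Illustration (all inputs assumed; none is in the documents)**

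For one baseline disorder, let p be the true persistence, f the share of persisting cases not affirmed on the screener, and o the share of those caught by the override. Assume that a persisting disorder is recognised once its section is administered. Then

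recorded remission = 1 − p × (1 − f × (1 − o)).

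*Unequal under-endorsement, same true persistence.* The spurious difference is p × (1 − o) × (f50 − f25).

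- Worked case: p = 0.5, f25 = 0.05, f50 = 0.15, o = 0. Recorded remission is 1 − 0.5 × 0.95 = 52.5% against 1 − 0.5 × 0.85 = 57.5%, a false difference of 5 points.
- Lower end: p = 0.5, gap in f of 0.05, o = 0 gives 0.5 × 0.05 = 2.5 points.
- Upper end: p = 0.6, gap of 0.15, o = 0 gives 0.6 × 0.15 = 9 points.
- If the override catches half (o = 0.5), that range halves to 1.25 to 4.5 points.
- If it catches all (o = 1), or if f25 = f50, the spurious difference is 0.
- If f25 exceeds f50, the sign reverses.

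*Equal under-endorsement, different true persistence.* The recorded difference is the true difference × (1 − f × (1 − o)). With persistence 0.6 against 0.5, f = 0.15 and o = 0, true remission is 40% against 50%. Recorded remission is 1 − 0.6 × 0.85 = 49% against 1 − 0.5 × 0.85 = 57.5%. Both rates are inflated, and the true difference of 10 points shrinks to 8.5.

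**The case against.** The strongest case on the other side has five parts.

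- **The rule has safeguards.** A reader might infer that any disorder not endorsed is recorded as absent without interview. The text does not support that: the same sentence lets the assessor probe suspected false negatives, and the notation cut-off-1 appears to mean a threshold lowered by one, so a patient must fall below a more inclusive gate before a section is skipped. This stands. It makes the problem smaller but does not remove it, because the override is discretionary and has no stated trigger.
- **The article says the method follows the instrument's instructions.** Those instructions are not shown, so no argument can rest on what they cover, in either direction. Following them would not make a patient-completed gate blind.
- **The mixture is disclosed.** The article calls the assessment self-report combined with interview and claims blinding only for the research assistant. This stands; nothing is misdescribed. The weakness lies in what that blinding can protect.
- **An interview also depends on the patient's answers.** Someone inclined to deny symptoms on a form may deny them in person. This stands, and it means the illustration overstates what the gate alone contributes. In an interview, however, the blinded assessor can probe and rate; a skipped section gives no such chance.
- **An article condenses the full protocol.** Detail on repeat interviews may sit elsewhere. But the point concerns a rule that the article states without limiting it to baseline, not one that it omits.

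**Conclusion.** The point holds in a limited form. By default, and subject to an override without criteria and an apparently lowered threshold, a disorder diagnosed at baseline is presumed absent at END or FU 12 m when a patient who knows the dosage no longer affirms it. Assessor blinding therefore covers the remission comparison only in part. That patients know their dosage is inferred from the session schedules.

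A reader might go further and conclude that remission is biased toward 50 sessions. The documents do not support this. Patients given more sessions might under-endorse out of expectation, or might endorse more because therapy has raised their self-awareness. Neither size nor direction can be derived. The 0 to 9 points come from assumed persistence of 50 to 60% and an assumed gap in under-endorsement of 0 to 15 percentage points, with 9 requiring that the override catch nothing.

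Only a secondary outcome is affected. The BDI-II and MINI-plus depression outcomes do not pass through this gate. This is a worthwhile, cheap improvement in outcome ascertainment, not a threat to the main result.

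**What to change.** Add one procedural sentence: at END and FU 12 m the blinded assessor administers the SCID section for every personality disorder diagnosed at that patient's baseline, whatever the screener shows. Keep the screener rule, with its override, only for disorders absent at baseline.

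The cost is a few more minutes per patient in an interview already scheduled with the same assessor, with no extra staff. The article reports that recruitment is ongoing, so the change can still apply to outcome interviews yet to be held. It does not remove all dependence on the unblinded patient, whose answers still inform the interview.
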